## 4 STATISTICAL METHODOLOGY

### 4.1 General Methodology

For continuous variables mean, Standard Deviation (SD), median, minimum and maximum will be presented, or median and Interquartile Range (IQR) as applicable, and for categorical variables number and percentage.

The baseline characteristics will be described; inferential statistics will be performed and interpreted descriptively only.

The confirmatory analyses will be only performed for:

1. Primary efficacy variable, impact of IP on severe ROP (comparison of event rates)
2. Secondary efficacy variable, impact of IP on overall levels of AA (mol%) continuously over time
3. Secondary efficacy variable, impact of IP on overall levels of DHA (mol%) continuously over time
4. Secondary efficacy variable, impact of IP on BPD (yes/no at PMA week 36, comparison of event rates)
5. Secondary efficacy variable, impact of IP on IVH (grade 0-4)

For those analyses the difference in the estimates and their 95% Confidence Intervals (CI) will be provided, and tests will be adjusted for multiplicity according to the fix sequential method as per the sequential order above. This methods allows for the significance mass of 0.05 to be inherited to the next variable in order and the testing is stopped when non-significance is achieved.

|                                     |  |                                    |               |
|-------------------------------------|--|------------------------------------|---------------|
| STATISTISKA KONSULTGRUPPEN          |  | Statistical Analysis Plan          |               |
| Protocol:
Mega Donna Mega |  | Protocol No:
MEGADONNAMEGA 16-7 |               |
|                                     |  | Version:
1.0                    | Page 17 of 21 |

Missing data will be handled according to the section 3.2.

All other analyses will be considered as exploratory, 95% CI will be provided for the difference between the groups and p-values will be given only for descriptive purpose.

All tests will be two-tailed and confirmed analyses will be conducted at 0.05 level applying fix sequential testing. All analyses will be performed using SAS software version 9.4 (SAS Institute Inc., Cary, NC, USA).

## 4.2 Patient Disposition and Data Sets Analyzed

The number of infants included in each of the ITT, PP and safety populations will be summarized by treatment group. The number and percentage of subjects randomized and treated will be presented. Subjects who completed the study and subjects who withdrew from study prematurely will also be presented with a breakdown of the reasons for withdrawal by treatment group for the ITT population.

## 4.3 Protocol Violations/Deviations

Major protocol deviations are those that are considered to have an effect on the analysis. A list of potential major protocol deviations will be generated programmatically from the data captured before the clean file meeting. The clinical monitors of the study will review the list and the finalisation of the major protocol deviations will be done at the clean file meeting.

The number of patients with major protocol deviations will be summarized per treatment group.

## 4.4 Demographics and Baseline Characteristics

Demographics and baseline characteristics will be summarized by treatment group for the ITT and PP populations and analyzed according to the methods described in section "General Methodology" above.

## 4.5 Prior and Concomitant Medications

Prior and concomitant medication will be summarized by higher level group (cortisone, inotropes, insulin, caffeine citrate, diuretics, and all medications linked to AEs, e.g. antibiotics) and generic term by treatment group for ITT population.

## 4.6 Efficacy Analyses

### 4.6.1 Primary Efficacy Analysis

The primary analysis in this study is incidence of sight-threatening (severe) ROP, i.e. ROP stage 3 or worse. Due to early deaths and early discontinuations in study the primary analysis will be performed using Poisson regression studying event rates, where deaths and early drop-outs are contributing as non-events with their follow-up time in the study. From this analysis Relative Risks (RR) and 95% CI for comparison between the groups will be presented along with the p-value. The primary analysis will be adjusted for stratification used in the randomization, i.e. adjusted for centre and GA categories as fixed effects, according to the guidelines issued by EMA (*Points to consider on adjustment for baseline covariates*).

The main analysis will be performed on ITT population. The sensitivity analysis will be performed on ITT population comparing cumulative incidence rates adjusted for death as

|                                     |  |                                    |               |
|-------------------------------------|--|------------------------------------|---------------|
| STATISTISKA KONSULTGRUPPEN          |  | Statistical Analysis Plan          |               |
| Protocol:
Mega Donna Mega |  | Protocol No:
MEGADONNAMEGA 16-7 |               |
|                                     |  | Version:
1.0                    | Page 18 of 21 |

competing risk, other drop-outs handled as censored in the survival analysis. Gray's test will be performed for this purpose. Moreover, the effect of the sensitivity analysis will be explained by Hazard Ratios (HR) with 95% CI obtained from Cox proportional hazards models. The primary analysis will also be performed on PP population as robustness analysis.

Graphically, cumulative incidence curves with 95% CI will be presented per treatment group.

The analysis will be considered confirmed if the p-value <0.05.

The impact of IP on primary variable will also be evaluated descriptively by centre and by GA categories, used in stratification of the randomization.

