#### 4 STUDY DESIGN

The study is a Randomized Intervention, Multi-Center Study to Determine the Role of Fatty Acids in Serum and Breast Milk in preventing Retinopathy of Prematurity. Subjects who meet all inclusion and none of the exclusion criteria will be enrolled into the study. Upon entry into the study, subjects will be randomized and given a unique subject number.

A randomized intervention study of 105+105 (number based on power analysis regarding up to date ROP frequency, see 5.1 and 11.1) infants without major malformations born with a gestational age less than 28 weeks + 0 days will be performed.

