### **11.1 Determination of Sample Size and Statistical Methods**

#### **Primary endpoint**

The mean incidence of any ROP in an age-matched population (22 weeks + 0 days to 27 weeks + 6 days of GA at birth) in Sweden during the years 2008 – 2012 is calculated to 42%. Assuming an alpha of 5%, a power of 80% and a 50% reduction in incidence of any ROP, i.e. from 42% to 22%, a sample size of 80 subjects per treatment group is required. The reduction in any ROP with AA:DHA supplementation is based on efficacy in previous publications (33).

A total of 105+105 subjects will be included to compensate for protocol violations (experience gained in pilot study) and drop-outs (e.g. a perinatal death rate of approximately 15% at these gestational ages).

After the first 10 subjects have been treated, we will perform pharmacokinetic analyses with respect to fatty acid concentrations in serum.

After the first 30 subjects have been treated and evaluated a safety data committee will perform an evaluation to confirm that the safety profile is acceptable and that the assumption of a reduction in ROP incidence is reasonable.

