### 1.3 Treatment Groups

A randomized intervention study of 210 infants in total, 105 in the Conventional (Clinoleic) group and 105 in the Treated (Clinoleic + AA:DHA) group.

Enteral supplementation with AA:DHA will start at second enteral feeding after birth and continue once daily to postmenstrual week 40 + 0. The supplementation will be delivered prior to feeding (0.1-1ml, according to dosing scheme, see Appendix A in the protocol). If the infant does not tolerate any enteral feeding, the supplement will be given as long as gastric retention is administered.

The intervention group will receive a daily dose of 100 mg AA/kg/day and 50 mg DHA/kg/day (Formulaid™ 2:1 DSM). Dose adjustment will be performed after the infant has regained its birthweight and weight gain results in an increase of 0.1 ml or more (see protocol Appendix A).

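### Siblings can be enrolled, but no confirmatory analysis handles within-family correlation and the documents do not say how siblings are allocated

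*Combined protocol and SAP*

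**What the plan says.** **Eligibility and recording.** The exclusion criteria (protocol 5.3) do not bar multiple births. SAP 3.1.1 lists a yes/no twin indicator among the baseline variables. No identifier linking siblings is described.

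**Allocation.** Protocol section 4: "Upon entry into the study, subjects will be randomized and given a unique subject number". Allocation comes through the online CRF within centre and gestational-age category, with 14+14 or 7+7 infants per cell. Nothing says whether siblings are allocated together, individually or to opposite arms.

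**Confirmatory analyses (SAP 4.1, 4.6.1, 4.6.2).**
- Severe ROP: Poisson regression, "adjusted for centre and GA categories as fixed effects".
- AA and DHA: MMRM with visit, treatment and the value at birth. Correlation is modelled within infant over visits only, and sandwich errors are used only if residual plots are unsatisfactory.
- BPD: Poisson regression.
- IVH grade: Mantel-Haenszel chi-square test.

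None has a family term or cluster-based variance. The clarifications appended to the SAP do not add one, and the sample-size text has no allowance for clustering.

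**The concern.** Siblings share a mother, nearly always a gestational-age stratum and centre, and usually breast milk. The protocol samples breast milk fatty acids and records maternal diet, so a shared maternal influence on AA and DHA is plausible from its own design. If outcomes within a family are correlated and the analysis treats infants as independent, the standard error no longer matches the true sampling variation.

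The direction depends on allocation: co-allocated siblings make intervals too narrow, split siblings make them too wide, and independently randomised siblings leave them about right. Testing is in fixed sequence and stops at the first non-significant result. A mis-sized standard error for ROP therefore also decides whether AA, DHA, BPD and IVH are tested confirmatorily at all.

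**Working it through.** **1. The plan's own figure.** Inputs: 42% versus 22% any ROP, alpha 5%, power 80% (protocol 11.1); "All tests will be two-tailed" (SAP 4.1). With unpooled variance:

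n = (1.960 + 0.842)² × (0.42×0.58 + 0.22×0.78) / 0.20² = 7.849 × 0.4152 / 0.04 = 81.5, so 82 per arm.

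The protocol says "a sample size of 80 subjects per treatment group is required". That agrees within 2, with no room for a clustering allowance. (The pooled formula gives 85.)

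**2. Variance factor for siblings.** Let f be the share of infants in twin pairs and r the intraclass correlation. Neither is in the documents; I assume f = 10–40% and r = 0.1–0.5. The variance of the treatment difference is multiplied by:
- same arm: 1 + f·r, i.e. 1.01 to 1.20
- independent: about 1
- opposite arms: 1 − f·r, i.e. 0.99 to 0.80

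For a test whose variance is otherwise correct, actual alpha = 2 × [1 − Φ(1.960/√factor)].

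| Allocation | f·r = 0.01 | f·r = 0.20 |
|---|---|---|
| Same arm | 5.1% | 7.4% |
| Independent | about 5% | about 5% |
| Opposite arms | 4.9% | 2.8% |

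This is the approximation for the AA and DHA models and the IVH test.

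**3. What the text implies about allocation.** If the 14+14 and 7+7 cells are exact and infants are allocated individually, a second sibling lands in the first sibling's arm with probability 13/27 (48%) or 6/13 (46%). The factor is 1 + f·r × (2 × probability − 1). At f·r = 0.20 that is 1 − 0.20/27 = 0.993 or 1 − 0.20/13 = 0.985, effectively neutral.

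**4. The Poisson test for ROP.** With equal follow-up, the model-based variance of the log relative risk is 1/x₁ + 1/x₀ (x = events per arm). The correct variance for a binary outcome subtracts 1/n₁ + 1/n₀, which multiplies it by (1 − p) under the null. At an assumed p = 30%, and at f·r = 0.20:
- same arm: true SE / model SE = √(0.70 × 1.20) = 0.917
- opposite arms: √(0.70 × 0.80) = 0.748

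The model-based SE is too large in both cases.

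Null simulation (40,000 trials, 210 infants, risk 32%, f = 40%, r = 0.5, unadjusted, equal follow-up), rejection at nominal 5%:

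| SE used | Same arm | Independent | Opposite |
|---|---|---|---|
| Model-based Poisson | 2.7% | 1.7% | 0.7% |
| Binomial | 6.8% | 4.7% | 2.8% |

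With no twins the Poisson SE gives about 1.7%.

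With 178 infants and same-arm siblings at f = 40%, r = 0.5, the Poisson test rejected 3.2% at 30% risk, and 4.1%, 4.5% and 4.6% at 20%, 15% and 10% risk. The offset shrinks as the event becomes rarer. At 10% the large-sample formula gives √(0.90 × 1.20) = 1.04, so almost nothing is left.

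**5. Does clustering by mother repair it?** Null simulations with 210 infants and 30% risk covered f/r = 0.2/0.2, 0.3/0.5 and 0.4/0.5 under all three allocations. The model-based Poisson test rejected 0.9–3.4%. The test with variance clustered by mother rejected 4.3–5.3%, and its SE was 8–25% smaller, matching the ratios 0.917 and 0.748 in step 4.

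**The case against.** The strongest reply is that the documents describe individual randomisation, under which ignoring siblings is about neutral; that centre and gestational age, two of the things siblings share, are already in the primary model; and that twin share, correlation and event risk are all assumed. A twin indicator shows that multiples are eligible, not that both siblings are enrolled or how many.

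Much of this stands. Independent allocation is the closest reading, and no passage supports family allocation. A reader might infer that the standard errors and p-values of all confirmatory tests are invalid, or that type I error for ROP exceeds 5%. The documents do not support either. Without the allocation rule even the direction is unknown, and for the Poisson test the excess model variance outweighs the sibling effect in the settings tried. Nor does separate randomisation make a correctly specified test conservative; that requires siblings to be placed in opposite arms.

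Three things remain. The Poisson offset comes from a second variance misspecification and leaves the primary interval mis-sized. It does not extend to AA, DHA or IVH. And the centre and gestational-age adjustment is specified for ROP; the AA/DHA model as written contains neither, and the IVH test names no stratification.

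**Conclusion.** The omission is real: siblings can enter, no confirmatory analysis handles their correlation, and the allocation rule is missing. The consequence is uncertain in direction and moderate in size. For AA, DHA and IVH, a nominal 5% test would run between roughly 2.8% (siblings split) and 7.4% (siblings together), and near 5% if they were randomised independently. These figures rest on an assumed twin share of 10–40% and correlation of 0.1–0.5; a higher correlation for fatty acids would widen the range.

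For ROP, no inflation was seen. The more likely fault is an interval that is too wide. That rests on a common event (the documents give no rate for stage 3 or worse), equal follow-up and no covariates in the simulations. BPD uses the same type of model, so the same reasoning applies while BPD is common. This is a cheap improvement to the plan, not a reason to reject its results.

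**What to change.** - **Data:** record a pregnancy (mother) identifier; a yes/no twin flag cannot link siblings.
- **SAP 4.6.1 and the BPD analysis in 4.6.2:** Poisson regression with cluster-robust (GEE sandwich) variance by mother. This addresses both the sibling correlation and the excess Poisson variance.
- **AA and DHA in 4.6.2:** add a random effect for mother to the MMRM.
- **IVH in 4.6.2:** use a cluster-adjusted test.
- **Design description:** report whether siblings were randomised together or individually.

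The cost is some SAP wording and a little code. Intervals may widen slightly for AA, DHA and IVH if siblings shared an arm. They are likely to narrow for the Poisson models if the events are common.

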#### 4.6.2 Secondary Efficacy Analyses

Confirmatory analyses of secondary variables:

1. The secondary efficacy analyses of fatty acid levels over time will be evaluated by applying MMRM with the change in level of fatty acids (AA and DHA respectively) from birth as dependent variable, and visit, treatment group as fixed effects, fatty acid at birth as fix adjustment variable, with repeated measures by visit applying the covariance pattern (compound symmetry, autoregressive, Toeplitz, unstructured, overall and applied by treatment group) that minimizes the Akaike's Information Criterion (AIC). From this model without an interaction term the overall effect of the IP will be retrieved, presented by adjusted means with 95% CI. The assumption of normally distributed residuals will be checked by reviewing the diagnostic plots. If not satisfactory the sandwich estimators for the standard errors (resulting in wider CIs) will be applied. Additional model for descriptive (exploratory) purpose will be performed including interaction term from which the impact of IP over time will be retrieved and presented graphically.
2. The secondary efficacy analysis of the impact of IP on BPD will be analyzed on ITT population including infants for which BPD was evaluated at 36 weeks PMA, deaths and other drop-outs will be handled as non-events. Poisson regression with log-link function, will be performed, resulting in RRs with 95% CI and associated p-value.
3. The secondary efficacy analysis of the impact of IP on IVH (grade 0-4) will be analyzed on ITT population using all infants that have evaluated IVH, missing data will be considered as non-events. Mantel-Haenszel Chi-square test will be performed.

Following secondary variables will be analyzed descriptively:

1. PDA will be analyzed using Fisher's Exact test. Proportion of patients with events and 95% CI will be provided.
2. NEC will be analyzed in the same way as the primary efficacy variable, applying Poisson regression. RR with 95% CI will be provided.
3. Growth development, by computing difference with 95% CI between treatment groups in BWSDS, BLSDS, HCSDS for studied time points, only on infants born GA $\geq$ 24 weeks. Individual growth curves will be created by GA week and sex, per treatment group and mean curve estimated per each subgroup of infants.

Main analyses will be performed on ITT population and robustness analyses on PP population. Sensitivity analyses performed on ITT population handling deaths and early drop-outs as per the section 3.2 will also be performed.

|                                     |  |                                    |               |
|-------------------------------------|--|------------------------------------|---------------|
| STATISTISKA KONSULTGRUPPEN          |  | Statistical Analysis Plan          |               |
| Protocol:
Mega Donna Mega |  | Protocol No:
MEGADONNAMEGA 16-7 |               |
|                                     |  | Version:
1.0                    | Page 19 of 21 |

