### 1.2 Study Design

This study is a randomized intervention, multi-center study to determine the role of fatty Acids in serum and breast milk in preventing ROP. Infants without major malformations born at a gestational age (GA) of <28 weeks +0 days will be included.

Randomization will be as follows; GA  $\leq$  24 weeks +6 days, n=84, GA 25 weeks +0 days to  $\leq$  26 weeks +6 days, n=84 and GA 27 weeks +0 days to  $\leq$  27 weeks +6 days, n=42 (in order to receive equal number of infants with conventional treatment and infants treated with AA:DHA supplementation in relation to morbidity outcome. In order to adjust for center variability each center (n=3) will recruit as follows; GA  $\leq$  24 weeks +6 days, n=14 (conventional) +14 (treated), GA 25 weeks+0 days to  $\leq$  26 weeks +6 days, n=14 (conventional) +14 (treated) and GA 27 weeks +0 days to  $\leq$  27 weeks +6 days, n=7 (conventional) +7 (treated).

Study Flow Chart

|                                                                                                                                                                     | d
a
y
0 | d
a
y
1 | d
a
y
2 | ho
ur
7
2 | d
a
y
4 | d
a
y
5 | d
a
y
6 | d
a
y
7 | d
a
y
14 | W
3 | W
4 | W
5 | W
6 | W
7 | P
M
A
30+
0
+-
24h | P
M
A
31+
0
+-
24h | P
M
A
32+
0+-
24h | P
M
A
33+
0+-
24h | P
M
A
34+
0+-
24h | P
M
A
35+
0+-
24h | P
M
A
36+
0+-
24h | P
M
A
37+
0+-
24h | P
M
A
38+
0+-
24h | P
M
A
39+
0+-
24h | P
M
A
40+
0+-
24h |

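### Among the five confirmatory tests only the primary adjusts for the randomisation strata (centre and GA category); the AA, DHA, BPD and IVH analyses name neither factor and may lose some power

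*Combined protocol and SAP*

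**What the plan says.** SAP 1.2 (and protocol section 4) sets targets by three GA bands within each of three centres, half to each arm, and gives the reason: "In order to adjust for center variability each center (n=3) will recruit as follows". SAP 4.6.1 treats both factors as stratification factors and cites EMA guidance: "The primary analysis will be adjusted for stratification used in the randomization, i.e. adjusted for centre and GA categories as fixed effects".

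SAP 4.1 lists five confirmatory tests in fixed order: severe ROP, AA, DHA, BPD, IVH. Testing stops at the first non-significant result, and "All tests will be two-tailed and confirmed analyses will be conducted at 0.05 level applying fix sequential testing".

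SAP 4.6.2 then specifies tests two to five:
- **AA and DHA:** a mixed model for repeated measures (MMRM) on change from birth, with "and visit, treatment group as fixed effects, fatty acid at birth as fix adjustment variable".
- **BPD:** "Poisson regression with log-link function, will be performed, resulting in RRs with 95% CI and associated p-value". No covariate and no variance estimator is named.
- **IVH, grades 0 to 4:** "Mantel-Haenszel Chi-square test will be performed". No strata are named.

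NEC, which is descriptive, is to be analysed like the primary variable and so inherits its adjustment. The clarifications appended to the SAP change the fatty-acid visits, the BPD definition, the competing-risk method and the growth analysis. None adds a centre or GA term. SAP section 6 says that the specified analyses follow ICH and EMA guidance on adjustment.

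**The concern.** Stratified randomisation removes chance imbalance in the strata, so the treatment estimate varies less from trial to trial. An analysis that leaves the strata out still counts the between-stratum variation as noise. Its standard error is then too large, and its test rejects less often than it should.

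The documents themselves suggest that GA matters. Protocol section 1 describes outcomes worsening as gestational age falls. The GA bands are there to balance the arms on morbidity, and the protocol's own growth model in 11.1 includes GA as a fixed factor. GA also affects what a visit means in the fatty-acid model, because early visits are timed from birth and later ones by postmenstrual age. An infant born at 27+6 reaches day 14 at 29+6, one day before the 30-week visit. An infant born at 22+0 reaches day 14 at 24+0, six weeks before it.

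At stake is power in a gatekept sequence: a miss at AA, DHA or BPD closes every later step.

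**Working it through.** **The plan's own figures.** The only power calculation is for any ROP, 42% against 22%, stated as 80 per arm. With unpooled variance: (1.960 + 0.842)² × (0.42×0.58 + 0.22×0.78) / 0.20² = 7.849 × 0.4152 / 0.04 = 81.5, so 82, close to the stated 80. It does not bear on this point. No rate, SD or power is given for AA, DHA, BPD or IVH. The strata add up: 3 centres × (28 + 28 + 14) = 210, or 42/42/21 per arm by GA band.

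All stratum effects below are assumptions.

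**AA and DHA.** Simplify the MMRM to a linear-model contrast. Let the strata explain a share R² of the variance left after the birth level, and let f = √(1 − R²). With balanced strata the true standard error is f times the one that the unadjusted model reports. Hence:
- CI width ratio = 1/f
- type I error = 2 × [1 − Φ(1.960/f)]
- power = Φ(2.802 − 1.960/f), where the adjusted test has 80%

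| R² | CI wider by | Type I error | Power (adjusted 0.80) |
|---|---|---|---|
| 0% | 0% | 0.050 | 0.800 |
| 5% | 2.6% | 0.044 | 0.785 |
| 10% | 5.4% | 0.039 | 0.769 |
| 20% | 11.8% | 0.028 | 0.729 |
| 30% | 19.5% | 0.019 | 0.677 |

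**IVH.** 6,000 simulated trials of 210 infants in nine strata, ordinal grade, treatment log-odds shift −0.7. The GA log-odds shift is 0, ±0.6 or ±1.2 between the outer bands and the middle one.

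| GA effect | Type I error, unstratified → stratified | Power, unstratified → stratified |
|---|---|---|
| None | 0.049 → 0.050 | 0.634 → 0.634 |
| Moderate | 0.041 → 0.046 | 0.632 → 0.649 |
| Strong | 0.032 → 0.052 | 0.607 → 0.667 |

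**BPD, model-based Poisson variance.** With equal arms in every stratum and a common risk ratio, the variance of the log risk ratio is 1/E₁ + 1/E₀ (expected events per arm) with or without stratum terms. For control risks 80/50/20%: E₀ = 42×0.8 + 42×0.5 + 21×0.2 = 58.8; at RR 0.7, E₁ = 41.2; SE = √(1/58.8 + 1/41.2) = 0.203. Simulation (1,500 trials) gives 0.204 both ways, and 0.210 both ways for 65/50/35%. Power is 0.36 in every case, so adjustment gains nothing.

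**BPD, robust (sandwich) variance, RR 0.7, same trials.**
- 65/50/35%: SE 0.158 → 0.154, power 0.622 → 0.651 (2.9 points).
- 80/50/20%: SE 0.150 → 0.138, power 0.683 → 0.749 (6.6 points).

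**BPD with deaths as non-events.** The SAP counts deaths this way, and protocol 11.1 expects about 15%. Assume deaths of 28/8/3% by GA band: (84×0.28 + 84×0.08 + 42×0.03)/210 = 31.5/210 = 15%. Deaths concentrated at low GA flatten the gradient in observed BPD. With robust variance and RR 0.72:
- 75/50/25%: power 46.4% → 48.5%; size 4.6% → 5.4%.
- 65/50/30%: power 41.7% → 42.8%.

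Adding assumed follow-up offsets gives gains of 2.6 and 0.8 points respectively.

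**The case against.** The strongest reply is that the loss is small, conditional and in the safe direction. Much of that stands.

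- No stratum effect is in the documents. The fatty-acid model already adjusts for the birth level, so only what GA or centre explains beyond it counts, and that could be nothing.
- For BPD and IVH the SAP is silent, not explicitly unadjusted; a Mantel-Haenszel test can be stratified. But silence leaves a confirmatory test open to later choice.
- Section 6 says the analyses aim to be conservative towards the product. BPD and IVH are tested only if severe ROP, AA and DHA all succeed.
- The appended fatty-acid clarification drops postnatal weeks 4 and 6 because their availability depends on GA. This removes part of the visit-timing problem, not all of it.

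A reader might go further in four ways that the documents do not support:
- *Only the primary analysis adjusts.* NEC inherits the adjustment; the statement holds only within the confirmatory list.
- *The unadjusted tests are biased or invalid.* In the calculations above they held their size or fell below it.
- *BPD loses 6 or 7 power points.* That needs a robust variance, which the SAP does not name, and a steep GA gradient that ignores the rule for deaths.
- *Fisher's exact test for PDA must also be replaced.* PDA is descriptive and outside the confirmatory sequence.

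**Conclusion.** The point holds as an inconsistency among the confirmatory tests. The primary is adjusted for centre and GA category; AA, DHA, BPD and IVH are not specified to be, although section 6 claims one standard of adjustment throughout.

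The consequence is conservatism and some lost power if the strata are prognostic, with a possible early stop of the sequence. Its size cannot be derived from the documents. On the stated assumptions it is about 0 to 12 points for AA and DHA (R² of 0 to 30%) and 0 to 6 for IVH. For BPD it is nil with model-based variance and about 1 to 7 with robust variance, nearer 1 to 3 under the assumed deaths. It is worth correcting because the correction is nearly free.

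**What to change.** In SAP 4.6.2:
- Add centre and GA category as fixed effects to the AA and DHA MMRM.
- Add both to the BPD Poisson model, and specify robust (sandwich) variance. Without that statement the BPD adjustment brings no gain.
- State that the IVH Mantel-Haenszel test is the row-mean-score form stratified by GA category and centre.

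Leave PDA as it is. If any factor is deliberately omitted, say so and give the reason.

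The cost is SAP wording and a few model terms. SAP 3.1.1 already lists GA and centre as baseline variables, and the primary model uses both. The change should be fixed before outcomes are seen by arm.
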